# The COMPASS-MS Study on Implementing Digital Assessment and Treatment for Psychological Distress in Patients With Multiple Sclerosis: Protocol for a Real-World Longitudinal Study

**DOI:** 10.2196/83416

**Published:** 2026-07-28

**Keywords:** digital health, mental health, depression, anxiety, psychological adjustment, psychological distress, multiple sclerosis, cognitive behavioral therapy, CBT

## Abstract

**Background:**

Comorbid anxiety and depression in patients with multiple sclerosis (MS) are common, conferring a greater risk of poorer outcomes and increased health care costs. Few MS services include scalable treatment pathways for psychological distress.

**Objective:**

This study aims to conduct a real-world longitudinal study evaluating the implementation and potential effectiveness of an integrated pathway involving digital screening for psychological distress and COMPASS-MS, a therapist-guided digital cognitive behavioral therapy tailored to the challenges of living with MS.

**Methods:**

This is a mixed methods, observational, real-world, longitudinal study being conducted in the United Kingdom. Routine mental health screening in the MS clinic will identify patients experiencing distress (using predefined clinical cutoffs), who will be assessed for eligibility for psychological treatment, including the COMPASS-MS program. Participants will receive COMPASS-MS online over approximately 12 weeks (including up to six 30-min therapist sessions). The implementation, reach, and adoption of the treatment pathway within a specialist MS service will be assessed using aggregate data on the uptake of mental health screening, eligibility, and consent rates for COMPASS-MS, as well as the number of COMPASS-MS sessions completed. Interviews with patients and health care professionals will primarily assess the scalability and potential or actual barriers and facilitators of the new pathway. Potential effectiveness will be assessed using participant questionnaires at preintervention and 12 weeks postintervention. The primary effectiveness outcome will be pre-post changes in distress (Patient Health Questionnaire Anxiety and Depression Scale scores). Quantitative data will be summarized using descriptive statistics and mixed effects models. Qualitative data will be analyzed using reflexive thematic and framework analysis.

**Results:**

Recruitment of both patients and health care professionals began in June 2024. For patients, recruitment was completed as of September 2025, including 82 participants. For health care professionals and stakeholders, as of September 2025, 7 had consented and completed interviews, and 13 more were expected to be recruited by August 2026. Data analysis has not yet started; however, quantitative results are expected by September 2026.

**Conclusions:**

The study findings will inform treatment pathways that can be incorporated into MS clinics and highlight adaptations or implementation protocols required to increase future scalability and effectiveness.

## Introduction

Multiple sclerosis (MS) is a chronic, incurable neurological condition characterized by the demyelination of the central nervous system. The majority of people living with MS are diagnosed with relapsing-remitting MS (~85%), which involves intermittent relapses or “flares” of new or existing symptoms, followed by periods of recovery or “remission” [1]. A smaller proportion, approximately 15%, have primary progressive MS [1]. Many with relapsing-remitting MS eventually transition to secondary progressive disease, after a median of 20 (range: 1‐51) years, in untreated cases [2]. People living with MS commonly experience diverse and unpredictable symptoms, including fatigue, mobility issues, and cognitive impairments. Unsurprisingly, psychological distress, including symptoms of depression and/or anxiety, is among the most common comorbidities in people living with MS [3]. Prevalence is estimated at 31% for depression and 22% for anxiety [4].

Psychological distress is associated with poorer clinical outcomes, including increased disease severity and disability [5,6], poorer quality of life [7], and reduced adherence to disease-modifying therapies [8]. It is also linked to increased health care usage and costs for health services [9]. Despite these consequences, MS treatment is largely focused on the biological aspects of the disease, and psychological comorbidities remain a substantial unmet need [10,11]. Evidence suggests that distress is often undetected or undertreated, with two-thirds of people living with MS who meet the criteria for depression receiving no medication or psychological support [12-15]. This gap persists despite the availability of reliable and brief screening tools, alongside expert consensus panels and people living with MS advocating for routine distress screening and support in MS clinics [16-18].

While both pharmacological treatment and psychotherapy show promise in addressing distress among people living with MS [19], evidence suggests that people living with MS prefer psychotherapy, demonstrating their inclination toward proactive support and skill-building to manage well-being [10]. Cognitive behavioral therapy (CBT) is recommended by the National Institute for Health and Clinical Excellence for treating depression and anxiety in the context of long-term conditions (LTCs), including MS [20]. CBT treatment protocols that are tailored to the challenges of living with MS appear to demonstrate larger treatment effects than traditional CBT [21], which reflects findings in other LTC populations, showing that LTC-tailored CBT increases treatment effect sizes for psychological distress alongside patient acceptability [22,23]. However, providing tailored CBT presents challenges for MS clinics due to cost, time, and workforce constraints.

Digitally delivered CBT presents a scalable solution. Digital CBT achieves similar effect sizes as face-to-face treatment while reducing costs and therapist time, as well as improving accessibility [24-27]. Researchers at King’s College London developed COMPASS, a therapist-guided, web-based CBT program designed to treat depression and/or anxiety in patients living with LTCs. COMPASS was based on the transdiagnostic model of adjustment to LTCs and targets mechanisms known to maintain depression or anxiety and prevent optimal psychological adjustment in people with LTCs [28].

The original transdiagnostic version of COMPASS was tested in a randomized controlled trial (RCT) compared with standard charity support [29]. This RCT, involving 4 distinct LTC populations (MS, inflammatory bowel disease, psoriasis, and kidney disease), demonstrated medium to large treatment effects on self-reported psychological distress, depression, anxiety, and illness-related distress across all LTCs at 12 weeks’ postrandomization [30]. However, exploratory moderation analysis suggested smaller effects for anxiety and illness-related distress in the MS subgroup compared with LTCs, indicating scope to further tailor the intervention for people living with MS and potential to boost the efficacy of COMPASS. Qualitative findings highlighted that people living with MS generally approved of COMPASS; however, they also desired more MS-specific content [31]. To address this, COMPASS was adapted for the population with MS (COMPASS-MS) using the person-based approach [32] and extensive patient and public involvement (PPI) [33]. A separate manuscript will detail the adaptation process [31].

Digital health tools are viable in MS care. For instance, a smartphone app for monitoring motor skills, mobility, and cognition was shown to be cost-effective through its impact on slowing disability progression, improving quality of life, and reducing medical costs [34]. To our knowledge, the cost-effectiveness of digital CBT tailored to patients with MS has not been assessed.

Moreover, while COMPASS shows promise, evidence of intervention effectiveness rarely translates to successful implementation; only 50% of psychological interventions from clinical research are embedded into routine usage [35], typically 17 years after development [36]. An existing service improvement project has investigated the implementation of a transdiagnostic version of COMPASS into a primary care, UK National Health Service (NHS) Talking Therapy setting [37]. However, the unique context and specific challenges for implementing COMPASS posed by a secondary care service for MS have not been explored. There is a need to evaluate COMPASS-MS not only for clinical effectiveness but also for implementation success, including barriers and facilitators to reach, adoption, acceptability, and/or scalability [38].

Qualitative research with people living with MS and health care professionals [39] suggests that effective mental health care for individuals with MS requires both internal service improvements (eg, better pathways for identifying and treating psychological distress) and external changes (eg, increased local funding). Developing and testing integrated pathways that include routine mental health screening and scalable, low-cost psychological support is an important step toward addressing these long-standing service gaps.

The overall aim of this mixed methods study is to evaluate the implementation and potential effectiveness of an integrated care pathway for treating psychological distress within 1 NHS neurology service for people living with MS. The integrated pathway includes routine mental health screening and COMPASS-MS, a digital therapist-supported CBT program adapted for MS. A nested qualitative study will additionally explore the barriers and facilitators to scaling the integrated pathway within and beyond the study site. In-depth interviews with stakeholders from the study site and approximately 6 to 8 additional neurology services will be conducted.

The study objectives were defined using 4 components of the RE-AIM (Reach, Effectiveness, Adoption, and Implementation) framework [40]. The specific objectives are as follows:

Reach: to assess the sociodemographic and clinical reach of the new integrated care pathway in the MS clinic.Effectiveness: establish the potential effectiveness of the treatment pathway for people living with MS and the service.Adoption: to qualitatively explore the barriers and facilitators to adopting the integrated pathway from the perspective of patients and health care professionals at the study site, as well as stakeholders in other NHS neurology services.Implementation: to explore the potential implementation of COMPASS-MS in routine practice, including engagement, adherence, and therapist fidelity.

## Methods

### Study Design

This real-world longitudinal, single-arm study includes 2 nested qualitative studies. Quantitative data will be collected at pretreatment and posttreatment (12 wk). This protocol is aligned with the SPIRIT (Standard Protocol Items: Recommendations for Interventional Trials) guidelines (Checklist 1), which has been adapted for single-arm, nonrandomized studies.

### Study Setting

This study will be conducted within a London-based outpatient neurology MS clinic. The MS clinic is a specialist service and provides care for approximately 1000 adults with MS who are aged 18 years or older. The clinic employs 5 consultants, 5 nurses, and 4 community MS nurses. Currently, psychological provision within the service is limited; however, the medical team liaises with a neuropsychiatrist who advises the team on addressing mental health needs.

### Study Participants

Patients with a diagnosis of MS, aged 18 years or older, who are experiencing psychological distress will be eligible for inclusion. Mental health screening and treatment will be available to patients who have an appointment at the MS clinic during the study’s implementation.

**Figure 1. F1:**
[figure not shown]
Referral, screening, and treatment pathway overview. ^a^The consent form will allow participants to opt in to a posttreatment interview. Participants were purposively sampled for the posttreatment interviews to capture the range of sociodemographic diversity and engagement with COMPASS-MS. GAD-7: Generalized Anxiety Disorder-7; MS: multiple sclerosis; NHS: National Health Service; PHQ-8: Patient Health Questionnaire-8; PTSD: posttraumatic stress disorder.

##### COMPASS-MS Intervention Inclusion Criteria

Patients will be eligible for COMPASS-MS if they are 18 years or older, have a diagnosis of MS, possess sufficient English language skills to interact with digital CBT, have access to a computer or device to complete the intervention, present with at least mild symptoms of distress, and demonstrate evidence of illness-related distress.

Patients will not be eligible if they have an active suicidal risk (recent suicidal intent and/or plans); are currently receiving psychological treatment; have a mental health presentation that is not related to MS; or have a health issue identified by a clinician that may be a barrier to using COMPASS-MS, such as substance dependency, a severe mental health condition (such as posttraumatic stress disorder), or severe cognitive impairment.

### Study Procedures

#### Procedure: Patient Participants

The route of routine screening (MyChart vs clinician referral) and whether a patient completes a psychological assessment will be pseudoanonymized, recorded, and shared with the research team. For patients who complete a psychological assessment, demographic information (age, gender, ethnicity, and index of multiple deprivation) and clinical information (depression, anxiety, cognitive impairment, and disability) will be collected to determine the appropriate treatment pathway (more details are given in the “Implementation Measures” and “Effectiveness Measures” sections).

Following patient screening and assessment, eligible and interested patients who have consented to share their contact details will be contacted by the research team. Patients will be emailed the information sheet and a link to the informed consent form. Upon receipt of consent, a link to the baseline questionnaire (pretreatment) will be sent. Following its completion, patients will be enrolled in COMPASS-MS. Patients will complete a follow-up questionnaire 12 weeks after baseline (posttreatment). All recruitment procedures will be conducted remotely via telephone or the Qualtrics online platform [44]. Pre- and posttreatment questionnaires will also be administered through Qualtrics. These questionnaires will assess the potential effectiveness of COMPASS-MS. Additionally, eligible patients will have the option to consent to participate in a qualitative interview study. A subgroup, purposively sampled to capture sociodemographic diversity and different levels of engagement with COMPASS-MS, will be invited to take part in an interview about their experience with the integrated pathway.

##### Nested Qualitative Interview Study: Inclusion Criteria

Eligible stakeholders will be those who engaged with the new care pathway at the study site, specifically those who have been involved in routine mental health screening, direct referrals to psychology, assessing patients as part of the new pathway, and providing COMPASS-MS therapist support. Furthermore, other stakeholders who work with people living with MS in the study site (eg, physiotherapists, occupational therapists, or commissioning bodies) will be eligible for inclusion.

Additionally, individuals who work with people living with MS in NHS trusts outside of the study site will also be eligible, including doctors, nurses, psychologists, occupational therapists, physiotherapists, and members of commissioning bodies. This will broaden the scope to include barriers and facilitators to implementation outside of the study site.

### Outcomes

Coprimary objectives are to explore the real-world implementation and effectiveness of a new integrated care pathway (mental health screening and COMPASS-MS treatment) in a specialist MS service, which treats approximately 1000 patients with MS. Our outcomes were defined using 4 components of the RE-AIM framework [40]. The specific outcomes are as follows:

#### Reach

Reach will describe the population who participate in the intervention. This will include the number, percentage, and characteristics of people living with MS who:

Complete routine screening and psychological assessment.Report clinical levels of psychological distress at assessment. Associations between distress and demographic or clinical characteristics will also be assessed.Meet the inclusion criteria for COMPASS-MS and consent to the COMPASS-MS study? Reach will also be assessed by comparing the demographic characteristics of patients who were referred to the study and those who consented to participate in COMPASS-MS.

#### Potential effectiveness

Potential positive impacts of the intervention on important outcomes will be assessed, at the level of the patient. These outcomes include:

What are the changes pre-post COMPASS-MS treatment for self-reported clinical outcomes (the primary effectiveness outcome is the change in psychological distress from baseline to 12-weeks, measured with an anxiety and depression composite score)? Additionally, secondary effectiveness outcomes will include depression, anxiety, illness-related distress, functioning, and quality of life).What are the changes pre-post COMPASS-MS in healthcare utilisation to explore potential cost-effectiveness?What are the potential mechanisms of change pre-post COMPASS-IBD (cognitive and behavioural responses to symptoms, acceptance of illness, intolerance of uncertainty, expression of emotion, health behaviours)?

The service-level impact of the intervention will also be assessed. These outcomes include:

How many people living with MS are subsequently identified as requiring more intensive treatment input after COMPASS-MS?What are the demographic and clinical characteristics of people living with MS who require more intensive treatment input following COMPASS-MS?

#### Adoption

Adoption will be explored *qualitatively* through themes on barriers and facilitators from patient and stakeholder interviews. Specifically:

What are the barriers and facilitators to *screening* and *treating distress using COMPASS-MS* from the *perspective of patients with MS and stakeholders* exposed to the care pathway?What are the barriers and facilitators to *scaling the pathway* to sites outside the study site?

#### Implementation

Implementation will explore how closely the intervention is received as intended. It will be assessed with the following questions:

What are the rates of adherent users, nonengagers, and dropouts? For adherence, we will report percentages of those adhering to the online component, the therapist component, and meeting the composite adherence definition (see the “Implementation” subsection in the “Implementation Measures” section).What is the therapist’s fidelity to the COMPASS-MS treatment?

### Implementation Measures

#### Reach

Data collected during screening and triage to determine appropriate treatment pathways will include the number, percentage, and characteristics of patients who (1) agree to and complete routine screening for psychological distress via MyChart; (2) receive a direct referral from a clinician for psychological distress after the identification of distress during a consultation; (3) complete psychological assessment; (4) are interested in receiving psychological support; (5) report clinical levels of psychological distress, depression, or anxiety at the time of assessment, and their sociodemographic predictors of these outcomes also evaluated; (6) report their distress as related to their experience with MS; (7) report the presence of active suicidal risk; (8) express interest in participating in the COMPASS-MS study; (9) meet the inclusion criteria for COMPASS-MS and provide consent to participate in the COMPASS-MS study, evaluating differences in demographic characteristics compared with those referred; and (10) receive COMPASS-MS but are subsequently identified during treatment as requiring more intensive treatment.

The characteristics that will be evaluated are as follows: (1) demographic information (age, gender, ethnicity, and index of multiple deprivation); (2) depression and anxiety measured using the PHQ-8 [42] and GAD-7 [43], respectively; (3) mild cognitive impairment assessed using the Montreal Cognitive Assessment telephone version [45,46]; and (4) Expanded Disability Status Scale score [47], which is clinician-reported based on an examination by a neurologist, with ranges from 0 to 10 in 0.5-unit increments, with higher scores reflecting greater disability.

For those who consent and complete the pretreatment questionnaire, data will be gathered on sociodemographic factors (age, gender, ethnicity, and index of multiple deprivation) and clinical factors (MS type, year of diagnosis, comorbidities, commonly occurring MS symptoms, relapse history in the last 12 wk, and medication to treat relapses).

#### Adoption

Patient interviews will be conducted remotely and will follow a semistructured interview guide. The interviews will focus on the experiences of people living with MS regarding MyChart mental health screening and clinician referral for support, study participation, and using COMPASS-MS.

Stakeholder interviews will assess perceptions of mental health screening and the treatment of psychological distress in people living with MS, as well as any barriers and facilitators to these processes. Additionally, for those exposed to MyChart screening and COMPASS-MS treatment, the interviews will explore the perception of implementing the integrated care pathway. The interview guide will be informed by the Normalization Process Theory [48] and the NASSS-CAT (Non-Adoption, Abandonment, and Challenges to Scale-up, Spread, and Sustainability) tool [49]. Stakeholder interviews will be conducted in-person or remotely.

### Effectiveness Measures

#### Primary Patient Effectiveness Outcome

Psychological distress will be measured pretreatment and posttreatment using the PHQ Anxiety and Depression Scale (PHQ-ADS) [50], which combines the PHQ-9 (9-item version) [51] and GAD-7 [43] into a 16-item measure of distress. A decrease of 4 or more points on the PHQ-ADS is considered a minimum clinically important difference [52], and total score cutoffs of 10, 20, and 30 indicate mild, moderate, and severe levels of distress, respectively [52].

#### Secondary Patient Effectiveness Outcome

Five secondary effectiveness outcomes will be collected as follows. First, *anxiety* will be measured using the GAD-7 [43], a 7-item self-report anxiety questionnaire. The questionnaire has a scale range of 0 to 21; higher scores indicate increased anxiety symptoms. Second, *depression* will be measured using the 9-item self-report PHQ [51]. This questionnaire has a scale range of 0 to 27; higher scores indicate increased depressive symptoms. Third, *illness-related distress* will be measured using the Illness-Related Distress scale [53]. The Illness-Related Distress scale is composed of two 7-item subscales (interpersonal and intrapersonal distress) answered on a 4-point scale. Each subscale ranges from 0 to 21, with higher scores indicating greater distress. Fourth, *social functioning* will be measured using the Work and Social Adjustment Scale, a 5-item measure of functional impairment [54]. The Work and Social Adjustment Scale has a scale range of 0 to 40, with higher scores indicating greater functional impairment. Finally, *health-related quality of life* will be measured using the EuroQol 5-Dimension Scale (EQ-5D-3L) [55]. The EQ-5D-3L includes 5 dimensions (range of scores, 1-3) that assess mobility, self-care, usual activities, pain or discomfort, and anxiety and depression. High item scores indicate poorer quality of life. The EQ-5D-3L also includes a visual analog rating scale (range: 0‐100), whereby higher scores reflect better global health.

Moreover, to assess potential cost-effectiveness, patients will be asked to self-report their health care usage. *Health service usage* will be explored through the 4 service use items from the Client Service Receipt Inventory [56]. These items ask participants to self-report whether they have visited their general practitioner, accessed psychologist or therapist support (outside of the study), visited a secondary care service, and accessed emergency care in the last 3 months.

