### Statistical Methods and Data Analysis

Most Reach and Implementation outcomes will be summarized descriptively. Categorical variables will be summarized with frequencies and percentages, while continuous variables will be reported as means and SDs or as medians with IQRs, depending on the distribution. Where relevant, rates (eg, eligibility, adherence) or mean differences (eg, change from baseline) will be presented alongside 95% CIs to quantify uncertainty in estimates. In the screened sample, differences in psychological distress, depression, and anxiety between key demographic characteristics (age, gender, and ethnicity) and any interaction effects will be examined using linear regressions. For between-group comparisons (eg, demographic and clinical differences between referred patients vs those who consent to COMPASS-MS and COMPASS-MS participants with baseline data only vs COMPASS-MS participants with complete data), chi-square test, Mann-Whitney *U* test, and two-tailed independent sample *t* tests will be conducted, depending on the distribution of the variable.

Potential effectiveness will be assessed using mixed effects linear regression, including a random intercept to account for repeated measurements within participants. Assessment time points will be modeled as dummy-coded covariates to estimate change from baseline, adjusting for demographic and relevant clinical variables. Interaction terms between time and covariates will be tested to explore whether the change from baseline differs across subgroups. Effect sizes will be reported as standardized mean differences, using the adjusted mean change from baseline from the mixed-effects models and the pooled SD (treating baseline as the control). Mixed-effects models will handle missing data using full-information maximum likelihood, under the missing-at-random assumption. Missing item-level data within self-report measures will be handled using proration when at least 50% of items are completed.

A per-protocol sensitivity analysis will be undertaken for potential effectiveness outcomes, restricted to participants who fully adhered to the treatment protocol (≥5 online sessions and attending ≥3 appointments). Moreover, moderator analyses are exploratory and will be conducted for the primary effectiveness outcome with the intention-to-treat sample to examine the heterogeneity of the treatment effect across MS subtype, age, gender, ethnicity, and education level.

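### Entry rules shift the baseline of two of the four service-use items, and a single arm cannot turn pre-post service use into evidence on cost-effectiveness

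*Protocol article*

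**What the plan says.** Under Potential effectiveness, the protocol article asks "What are the changes pre-post COMPASS-MS in healthcare utilisation to explore potential cost-effectiveness". The Secondary Patient Effectiveness Outcome section gives the same purpose: "to assess potential cost-effectiveness, patients will be asked to self-report their health care usage". Four items from an existing inventory are used. Patients "self-report whether they have visited their general practitioner, accessed psychologist or therapist support (outside of the study), visited a secondary care service", and whether they "accessed emergency care in the last 3 months".

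Two entry rules bear on these items. Under Study Participants, screening and treatment are "available to patients who have an appointment at the MS clinic" during the study. Under COMPASS-MS Intervention Inclusion Criteria, patients who "are currently receiving psychological treatment" are not eligible.

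Study Design describes one arm with two time points, and Study Procedures puts follow-up 12 weeks after baseline. Statistical Methods and Data Analysis says "Potential effectiveness will be assessed using mixed effects linear regression", with effect sizes given as standardized mean differences. Limitations warns that, without a control group, changes in distress cannot be firmly attributed to the intervention. It does not mention service use or cost.

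**The concern.** A before-after comparison is interpretable only if both recall windows sample the patient's usual behaviour. For two items the baseline window does not.

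- **Secondary care.** Patients reach the study around an MS clinic appointment, either through app screening ahead of it or through referral by a clinician. The baseline window therefore tends to include that visit. Nothing requires a visit in the follow-up window.
- **Therapist support outside the study.** Patients in therapy at entry are removed. The article describes no such restriction after enrolment, so use can drift back towards its usual level. Some patients may also be identified as needing more intensive treatment, which could raise this item as a result of the pathway itself.

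A fall in secondary-care use could then be taken for a saving, and a rise in outside therapy for added demand, when either may only reflect how patients were selected. The cost-effectiveness purpose adds a separate problem: with one arm there is no incremental cost and no incremental effect, whichever items are used.

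**Working it through.** **The plan's own figures.** The article gives no expected rate, precision or power for service use. Its one detectable effect concerns the primary outcome and reproduces: (1.960 + 0.842)/√75 = 0.32, and d = 0.35 corresponds to (2.802/0.35)² ≈ 64 completers. It says nothing about these items.

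**Inputs from the protocol.** Four items, 3-month recall, follow-up at 12 weeks, one arm, target 75, 82 recruited, α = .05 (taken as two-sided).

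**Assumptions.** Usual use rates are not given, so a range is shown. I take 66 complete pairs, about 80% of those recruited (0.80 × 82 = 65.6). Baseline and follow-up answers are independent, the items are yes/no, and the treatment effect is zero.

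**Method.** Let b and f be the proportions answering yes at baseline and follow-up. A patient changes from yes to no with probability b(1 − f), and from no to yes with probability (1 − b)f. The expected change is f − b. The chance that an exact McNemar test gives p < .05 is summed over the binomial distribution of discordant pairs.

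| Item | b → f | yes→no | no→yes | Change (points) | Chance of p < .05 |
|---|---|---|---|---|---|
| Secondary care | 95% → 95% | 0.0475 | 0.0475 | 0 | 1% |
| Secondary care | 95% → 90% | 0.095 | 0.045 | −5 | 11% |
| Secondary care | 95% → 85% | 0.1425 | 0.0425 | −10 | 37% |
| Secondary care | 90% → 70% | 0.27 | 0.07 | −20 | 77% |
| Secondary care | 95% → 60% | 0.38 | 0.03 | −35 | >99% |
| Therapist support | 3% → 10% | 0.027 | 0.097 | +7 | about 24% |
| Therapist support | 0% → 10% | 0 | 0.10 | +10 | 66% |
| Therapist support | 0% → 15% | 0 | 0.15 | +15 | 94% |

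**Hand check of the 0% → 10% row.** No one can move from yes to no, so with m changers p = 2 × 0.5^m. That is 0.0625 for m = 5 and 0.031 for m = 6. Significance needs at least 6 of 66 patients, and P(Bin(66, 0.10) ≥ 6) = 0.66.

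**Sensitivity to the number of pairs.** With 75 and 82 pairs, 90% → 70% gives 83% and 86%, and 0% → 10% gives 77% and 84%.

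**Sensitivity to multiplicity.** The plan applies Holm-Bonferroni to secondary outcomes and mechanisms. Suppose it covers these items in a family of nine (five secondary outcomes plus four service items, an assumption). The strictest step is .05/9 = 0.0056. With 66 pairs, 90% → 70% drops to 45%, 95% → 85% to 11%, and 0% → 10% to 21%. The correction makes a significant result less likely but leaves the expected change, and so the bias, as it was.

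**What a yes/no item can carry.** If visits were Poisson (an assumption), halving the mean from 2 to 1 would move any use from 1 − e⁻² = 86% to 1 − e⁻¹ = 63%. The answer does not give a number of contacts to cost.

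**The case against.** The strongest reply is that a reader might infer that service use as a whole is fixed by entry, that secondary-care use can only fall and therapist use can only rise, and that the study will report the result as a cost-effectiveness finding. The documents do not support that.

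- No entry rule sets GP or emergency use, so at most two of four items are affected.
- App screening comes before the appointment. Telephone assessment, consent and the baseline questionnaire follow, with no stated interval. The clinic visit may fall before, inside or after the baseline window, and for patients whose visit comes after baseline the bias reverses.
- The secondary-care item is not confined to the MS clinic. If usual use is near 100%, little artefact remains.
- The exclusion covers current therapy. Therapy that ended within the previous 3 months still counts as use, so a 0% baseline is an extreme case.
- The yes/no format is inferred from how the article describes the items. The full form may record counts.
- The article speaks only of exploring or assessing potential cost-effectiveness. It plans no cost-effectiveness ratio, gives priority in interpretation to the primary outcome and core implementation outcomes, and says randomised trials are needed.
- The mixed linear model is described for effectiveness outcomes generally. Item-level models may sit in an analysis plan that is not shown.

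All of this stands, and it limits both the wording and the weight of the point. Three things remain. The entry rules push two baselines in directions that can be named beforehand. A single arm provides no increment in cost or effect. The stated limitation is confined to distress.

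**Conclusion.** The concern holds for the secondary-care and therapist-support items. Their pre-post change could show a fall and a rise respectively without any treatment effect. Under the rates tried, the chance of a nominally significant result runs from about 11% to over 99% for secondary care and from about 24% to 94% for therapist support. These figures rest on assumed use rates, 66 complete pairs, independent answers and unadjusted α = .05, so they show that the size is unknown rather than that it is large.

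For GP and emergency use there is no entry-rule bias, only the missing comparator. For all four items, pre-post service use cannot support a cost-effectiveness conclusion, and no later analysis plan could supply the missing arm.

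This is a secondary, exploratory outcome that leaves the primary result untouched. It should be fixed, but it is not a critical flaw.

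**What to change.** 1. Report secondary-care and therapist-support use descriptively at each time point, with no pre-post test and no claim of effect. If the form allows, leave the index MS clinic visit out of the secondary-care item. State that the entry rules influence both baselines.
2. If the items are yes/no as the article describes them, analyse GP and emergency use as paired binary outcomes, giving a risk difference with 95% CI in place of the linear model and standardized mean difference.
3. In both places where cost-effectiveness is named as the purpose, say instead that service use will be described.
4. Extend the no-control-group limitation from distress to service use.

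The cost is wording and a different summary for a few items. No new data are needed, and the article says that analysis had not started. What is lost is the cost-effectiveness purpose, which this design could not deliver.
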